## Abstract

**Background:**

Accurate diagnosis of preterm labour is needed to ensure correct management of those most at risk of preterm birth and to prevent the maternal and fetal risks incurred by unnecessary interventions given to the large majority of women, who do not deliver within a week of presentation. Intervention “just-in-case” results in many avoidable admissions, women being transferred out of their local hospital unnecessarily and most women receiving unwarranted drugs, such as steroids and tocolytics. It also precludes appropriate transfers for others as neonatal cots are blocked pre-emptively, resulting in more dangerous ex-utero transfers. We have developed the QUiPP App which is a clinical decision-making aid based on previous outcomes of women, quantitative fetal fibronectin (qfFN) values and cervical length. It is hypothesised that using the QUiPP app will reduce inappropriate admissions and transfers.

**Methods:**

A multi-site cluster randomised trial will evaluate whether the QUiPP app reduces inappropriate management for threatened preterm labour. The 13 participating centres will be randomly allocated to receive either intervention or control. If the QUiPP app calculates risk of delivery within 7 days to be is less than 5%, clinicians are advised that interventions may be withheld. Women’s experience of threatened preterm labour assessment will be explored using self-completed questionnaires, with a subset of participants being invited to semi-structured interview. A health economics analysis is also planned.

**Discussion:**

We hypothesise that the QUiPP app will improve identification of the most appropriate women for admission and transfer and ensure that therapies known to reduce risk of preterm neonatal morbidities are offered to those who need them. We will determine which women do not require these therapies, thereby reducing over-medicalisation and the associated maternal and fetal risks for these women. The findings will inform future national guidelines on threatened preterm labour. Beyond obstetrics, evaluating the impact of an app in an emergency setting, and our emphasis on balancing harms of over-treatment as well as under-treatment, make EQUIPTT a valuable contribution to translational medicine.

**Trial registration:**

The EQUIPTT trial was prospectively registered on 16th January 2018 with the ISRCTN registry (no. 17846337).

## Background

Women with symptoms of preterm labour have long posed a diagnostic challenge for clinicians concerned with managing the risks of preterm birth when the reality is that most women will not deliver imminently [1]. Various prediction methods are available to direct interventions that delay or ameliorate the consequences of preterm birth (e.g. in-utero transfer, tocolysis, antenatal corticosteroids). However these interventions have psychological, economic and clinical implications if given unnecessarily.

In light of recent UK guidance to treat all women in threatened preterm labour (TPTL) prior to 30 weeks [2], most of these women are likely to be admitted. However, the majority of women presenting with symptoms of preterm labour will not deliver in seven days [1].

## Risks associated with antenatal corticosteroids

Clinicians are familiar with steroid-induced glucose intolerance in the mother, necessitating insulin/dextrose infusions and prolonged admissions. However, fetal exposure to steroids has become the over-arching concern. There is a significant reduction in infant birthweight of those women exposed to antenatal corticosteroids who deliver more than seven days after the first dose, compared to those receiving no treatment (mean difference 147 g, 95% CI -291.97 to − 2.05 g) [3]. Infants exposed to steroids are at increased risk of neonatal hypoglycaemia (1.61 CI 1.38–1.87) and are significantly more likely to be in the lower quartile of academic ability (*p* = 0.01) (ARR 9.2–17.7% to 8.5%) [4]. There is biological plausibility supporting the latter finding given evidence of decreased brain growth in preterm and term infants exposed to antenatal corticosteroids in animal studies [5]. There is also evidence that fetal exposure to glucocorticoids modifies fetal hypothalamic-pituitary-adrenal function, which is associated with increased risk of cardiovascular and metabolic diseases in adulthood [6, 7]. Structural development of the brain may also be affected by steroid exposure, such as impaired cortical folding [8] and cortical thinning [9].

## Risks associated with unnecessary in-utero transfer

Appropriate antenatal in-utero transfer (as opposed to ex-utero) is essential to avoid the significant increases in neonatal morbidity and mortality associated with postnatal transport of preterm infants [10]. In some units a treat-all policy for threatened preterm labour would dramatically increase the number of such transfers. The implications of this far exceed the ambulance transfer costs: being transferred to another hospital unit (out of area) is associated with a significant stress and expense for the parents and family [11]. There is an immediate clinical burden of transfer arrangements, which involves a number of on-call obstetric, neonatal and midwifery teams and takes an average of 340 min to complete [12]. This does not include the return journey time of the transferring midwife. Paradoxically, unwarranted antenatal transfers may increase more dangerous postnatal transfers by impairing efficient management of neonatal cots (i.e. cots reserved for babies that do not actually deliver preterm). With these neonatal cots blocked, infants of women in true preterm labour are only able to be transferred postnatally.

## Maternal risks

Hospitalisation also increases the risks of venous thromboembolism, hospital-acquired infections and the psychological strain for the mother.

Our research group has developed the QUiPP App, which improves prediction of preterm labour by combining clinical parameters and calculates risks more precisely from continuous variables, to better assess risk [13–15]. It utilises quantitative fetal fibronectin (qfFN) (a protein released into the vagina at high concentrations during preterm labour), the use of which has been developed by our group [13–15]. In a prospective observational study of 300 women, we reported a negative predictive value (NPV) for qfFN at < 10 ng/mL of 98.2%, and a positive predictive value (PPV) for delivery < 34 weeks at a 200 ng/mL threshold of 37% [13]. The value is limited by these arbitrary thresholds, and we showed that improved prediction can be obtained by interrogating the data across the whole qfFN range i.e. better sensitivity and “rule out” at low levels and improved specificity and “rule in” at high levels. We combined qfFN and cervical length measurements (also as a continuous variable) to improve the prediction further in 1249 asymptomatic women [14]. We then created a predictive model from a prospective observational dataset of 382 women with TPTL to provide an individualised risk of delivering within 1/2/4 weeks and before 30/34/37 weeks [15]. The accuracy of the model was further confirmed using a validation set and performance reliability demonstrated by comparison of expected and observed sPTB rates (*p* > 0.05). Receiver operating characteristic areas in the validation set differed from the training set by amounts between − 0.04 and + 0.02 [15]. The model was subsequently updated on a larger dataset comprising 1032 women presenting with symptoms of TPTL, and this is the analysis that is incorporated into the latest version of the QUiPP app.

In terms of guiding management decisions, the majority of cases are assigned a very low-risk (< 1%) by QUiPP app, which clearly indicates a “no admit” strategy. In EQUIPTT, we provide a guidance threshold of 5% risk of delivery within seven days for intervention, based on our previous published work [16]. However, given the other multiple variables that contribute to this decision (such as gestational age), and our intention for the QUiPP app to be a tool to help clinicians make their own decisions, we have refrained from dogmatic recommendation based on absolute thresholds.

We also want to establish if use of the QUIPP app reduces women’s anxiety and/or helps her to come to decisions about her care that she is happy with. Women may have different preconceptions about the significance of symptoms of TPTL and varying perspectives on consequences of admission and or transfer, such as financial anxieties and separation from family, friends and other children [11]. Furthermore, the use of an app to guide clinical management is new to healthcare practice. Given the importance of shared decision-making emphasized by the Montgomery ruling [17], women’s views regarding its application in threatened preterm labour will be central to the future development of the QUIPP app.

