### Sample size

For inappropriate admission decisions, a total sample size of 580, approximately 50 recruits per site, was calculated. Data from our group’s ongoing prospective observational study into the ability of qfFN to predict preterm birth in symptomatic women (PETRA REC Ref. 14/LO/1988) has allowed us to estimate the likely treatment effect for the intervention reducing inappropriate admissions from 25 to 10% and intra-class correlation 0.030. Based on 13 clusters this treatment effect requires approximately 580 for 80% power. We are aware that a larger number of centres would also be preferable, but believe 13 is adequate and at the limit of what is currently feasible.

For our qualitative questionnaires, we have estimated a target recruitment of 300 participants, 25 recruits per site, allowing for non-compliance and data collection errors. Based on previous research involving visual analogue scale (VAS) scores [19], a total sample size of 272 was required at standard levels of significance (alpha = 0.05 two-sided) to achieve 90% power to detect a 10% difference in mean VAS scores between hospitals with and without the intervention.

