### Randomisation

Randomisation is at the cluster level. Centres have been randomly allocated to receive either intervention or control. Due to there being an odd number of centres, seven sites were allocated to one group and six to the other. Minimisation of the randomisation list was not appropriate for this design but the imbalances between three levels of NICU facility at intervention and control sites were small (4:3, 3:2, and 0:1). TPTL rates were known for 10 sites and the difference between the average rates at control and interventions sites were within chance (72 and 89%).

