### Implementing the QUiPP app intervention

In each phase, each cluster will recruit consecutive women with singleton or twin pregnancies presenting between 23^+ 0^ and 34^+ 6^ weeks presenting with symptoms of preterm labour. Eligible participants will be identified at labour ward and day assessment triage by the direct care team and local research support teams. Inclusion and exclusion criteria are defined above.

All sites will receive training on the use of the QUIPP App and management guidance prior to its introduction, and periodically throughout the trial at peaks of staff turnover. This training will be delivered by the trial team at different times and locations to suit each site, for example, at departmental audit meetings and staff induction. Training will be delivered via clinical vignettes which provide opportunity for the clinicians to use the app in a training environment. Aide-memoires such as lanyards and pens are provided to each site to encourage use of the app. The doctor/midwife assessing the woman inputs the gestation, previous history of late miscarriage or preterm birth, quantitative fetal fibronectin value and/or ultrasonic cervical length into the app and the app provides % risk of delivery within 1/2/4 weeks and before 30/34/37 weeks. The exact thresholds for admission or treatment are gestation-dependent and may need to be tailored to individual circumstances. However as a recommendation, our guidance will suggest a 5% risk of delivery within 7 days as threshold for antenatal corticosteroid administration, admission, and/or in-utero transfer. Ultimately however the management decisions following the knowledge provided by the QUIPP app will remain the clinicians’ responsibility. A feedback option is available on the app to directly contact the trial team with specific non-clinical queries. Incentives and competitions will also aim to increase recruitment for the qualitative recruitment.

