### Outcomes

#### Primary outcomes

Our primary outcome of inappropriate management for threatened preterm labour is defined by:number of inappropriate admission decisions: admitted and delivery interval > 7 days OR not admitted and delivery interval < 7 daysandnumber of inappropriate in-utero transfer decisions/actions: in-utero transfers that occurred or were attempted > 7 days prior to delivery, and ex-utero transfers within 24 h that should have been in-utero (attempted and non-attempted)

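### The admission part of the primary outcome leaves a delivery interval of exactly 7 days in neither limb, so a non-admitted woman who delivers on day 7 is not counted as a missed delivery (minor)

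*Protocol article*

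**What the plan says.** The guidance is worded the same way throughout the article. The Background (under Maternal risks) has "we provide a guidance threshold of 5% risk of delivery within seven days for intervention". The Methods paragraph of the abstract has "If the QUiPP app calculates risk of delivery within 7 days to be is less than 5" per cent, in which case clinicians are told that interventions may be withheld. Implementing the QUiPP app intervention has "a 5% risk of delivery within 7 days as threshold for antenatal corticosteroid administration, admission, and/or in-utero transfer", and the Discussion repeats this. None of these places writes the horizon as an inequality.

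The Primary outcomes section does use inequalities. Its admission component has two limbs: admitted with an interval strictly above 7 days, and not admitted with an interval strictly below 7 days. Its transfer component counts "in-utero transfers that occurred or were attempted > 7 days prior to delivery", together with certain ex-utero transfers defined by a 24-hour window. Under Secondary outcomes, every component of the primary outcome is also analysed separately.

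**The concern.** The two limbs of the admission component should divide the time axis between them: an admission is wrong on one side of the boundary, and a non-admission is wrong on the other. With a strict inequality on both sides, day 7 belongs to neither, so no decision can be inappropriate for a woman who delivers then.

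The guidance treats delivery within 7 days as the event of interest, and in ordinary use that includes day 7. The admission and in-utero transfer limbs agree with this, because both start to count only after 7 days. The non-admission limb alone stops short of day 7. At stake is a small under-count of missed deliveries, a component reported in its own right, and a mismatch between the event that the app predicts and the event that the trial scores.

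**Working it through.** **The plan's own figure.** The Sample size section assumes "reducing inappropriate admissions from 25 to 10% and intra-class correlation 0.030" and states "Based on 13 clusters this treatment effect requires approximately 580 for 80% power". Under Randomisation, "seven sites were allocated to one group and six to the other". A two-sided alpha of 0.05 is stated only for the questionnaire calculation and is assumed here for the primary outcome.

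- Individually randomised total for 25% against 10% at 80% power, equal arms: 200, or 226 with continuity correction.
- Design effect 1 + (m − 1) × 0.03. With m = 580/13 = 44.6 it is 2.308; with m = 50 it is 2.47.
- Totals with normal quantiles: 200 × 2.308 ≈ 462 and 200 × 2.47 = 494; with continuity correction 226 × 2.308 ≈ 522 and 226 × 2.47 ≈ 558.
- Power at 580 with 6 control and 7 app clusters, unpooled variance: effective size 580/2.308 ≈ 251, split about 116 and 135. The standard error is √(0.25 × 0.75/116 + 0.10 × 0.90/135) ≈ 0.048. With a t reference on 13 − 2 = 11 degrees of freedom, power is 81.5%.

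The stated 580 is thus consistent with 80% power. The 25% and 10% are assumed rates, and the day-7 boundary is not an input, so the calculation does not change with the fix.

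**The rule, cell by cell.**

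| Interval to delivery | Admitted | Not admitted |
|---|---|---|
| Below 7 days | not inappropriate | inappropriate |
| Exactly 7 days | not inappropriate | not inappropriate |
| Above 7 days | inappropriate | not inappropriate |

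If the event is delivery by day 7 inclusive, the middle-left cell is right and only the middle-right cell is misfiled.

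**Size, if the interval is in whole days.** The documents give neither the share of women who deliver on day 7 nor the number sent home who deliver within 7 days. Both are assumed here.

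- Share of day 7 among days 0 to 7, with daily weights w(d) = 0.5^(d/h): share = w(7) / Σ w(d).
  - Constant rate: 1/8 = 12.5%.
  - Rate halving every 3 days: 0.198/4.084 = 4.9%.
  - Rate halving every 1.5 days: 0.0394/2.635 = 1.5%.
- Assume that 1% to 3% of 580 women are sent home and deliver within 7 days: 5.8 to 17.4 women.
- Uncounted: 5.8 × 0.015 ≈ 0.1 to 17.4 × 0.125 ≈ 2.2 women, that is, about 0 to 2.
- As a share of all women, the upper end is 3% × 12.5% = 0.375 percentage points. If every one of these women were in the app arm (580 × 7/13 ≈ 312 women), it would be 2.2/312 ≈ 0.7 points, against a planned difference of 15.

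A wider assumption bounds everyone on the boundary, whatever the decision. If 2% to 10% of all women deliver within 7 days and 5% to 14% of those do so on day 7, then 0.1% to 1.4% of 580, roughly 1 to 8 women, have an interval of exactly 7 days. Only those not admitted would be reclassified.

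**Size, if the interval is in hours.** An interval of exactly 168 hours is practically impossible, and the gap has no effect.

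**The case against.** The case against has several parts.

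- **The unit is not stated.** The transfer component uses a 24-hour window, so the interval may well come from dates and times. Gestation is given in weeks and days, which makes whole days plausible too, but neither is fixed. This stands, and the point is conditional on it.
- **The app's boundary is not shown.** The article says within 7 days, or within one week, and never gives the inequality behind the model. If the event were strictly below 7 days, the misfiled cell would be the admitted woman who delivers on day 7. This also stands. In whole days, though, one limb is misfiled on either reading, and the transfer limb supports the inclusive one.
- **Tie-handling belongs in the analysis plan.** This does not stand as an answer. The article states the inequalities outright, and the objection is to what they say. The unit could properly be given in the analysis plan.

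A reader might infer more than the documents support:

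- **That such a woman is scored as correctly managed.** The outcome has no such category; she is simply not counted as an inappropriate admission decision. She could still be counted under the ex-utero transfer limb.
- **That the rule biases the comparison towards the app.** On the inclusive reading it can only drop missed deliveries, but it applies equally in both arms. Only a between-arm difference in a handful of women could matter, and the documents give no basis for estimating one.
- **That the main safety signal is compromised.** The protocol does not give this component that role. Neonatal death, neonatal intensive-care admission and ex-utero transfer within 24 hours are separate secondary outcomes, and the data monitoring committee reviews adverse neonatal outcomes. None of these uses the 7-day boundary.

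**Conclusion.** The point holds as a minor defect in the outcome definition. As written, an interval of exactly 7 days is inappropriate under neither admission limb, which does not fit guidance built on delivery within 7 days or the two limbs that place day 7 inside the window. If intervals are in whole days and the horizon includes day 7, the missed-delivery component is under-counted by about 0 to 2 of 580 women on assumed rates. The effect on the composite is negligible, at under 0.4 percentage points overall. The sample size and power calculation is untouched. If intervals are in hours, there is no practical effect. No claim of material bias or loss of safety information follows.

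**What to change.** In the Primary outcomes section, change the non-admission limb to a delivery interval of 7 days or less (≤ 7), and keep more than 7 days for admissions and in-utero transfers. State whether the interval is in whole days or hours and how it is derived. Confirm that the boundary is the one used in the app's 7-day prediction, so that the predicted and scored events agree.

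The cost is one symbol in the definition and in the derivation code, plus a sentence on the unit. It needs no new data and no change to the sample size, and it concerns outcome scoring only. The count of inappropriate decisions may rise very slightly. The change should be made before outcomes are derived.

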## Methods/design

### Trial objectives

Our aim is to evaluate the ability of the QUIPP app to reduce inappropriate management of TPTL. This will externally validate the prediction model, assess its success as a clinical decision making tool, and measure its potential cost-saving impact in the emergency obstetric setting.

#### **Hypothesis:** The implementation of the QUIPP app and management algorithm will decrease inappropriate management for TPTL

### Trial design

EQUIPTT is a cluster randomised controlled trial (incorporating a parallel group design) across 13 obstetric centres. This design was chosen as for this scale of protocol intervention (in an emergency situation), it would be challenging to randomise at participant level, affecting uptake and generalisability of the findings, and individual clinicians cannot be randomised to varying decision-making with individual patients.

The pragmatic approach was taken to introduce the QUIPP app to entire hospital antenatal units, as standard practice for all clinicians, and all affected pregnancies. Using this parallel cluster studies have the added value of limiting the time-bias which occurs with a stepped wedge design. Also, unlike in a crossover design, the intervention does not need to be retracted from the cluster, avoiding contamination bias. Individuals within a cluster tend to have more similar outcomes than across clusters. The similarity in the outcomes of individuals within a cluster within a time period is typically measured by the within-cluster within-period intra-cluster correlation coefficient. If this is not factored into the power calculation and analysis, the effectiveness of the intervention may be exaggerated [18].

All 13 centres will provide data related to the principal outcome under their current practice in a six-week pre-intervention data collection period. Following randomisation, the centres will use intervention (using the QUiPP app) or control (routine management) for a nine-month analysis period. In the final phase of the trial, the intervention will be introduced in the 6 control units. Following this, data will be collected for a further six weeks across all 13 sites, in order to equally incentivise all sites to participate. The QUIPP app approach will be adopted as standard practice in all sites if successful. A list of the study sites is available from the authors on request.

An health economics analysis will also be conducted; this will involve a cost-minimisation and cost-consequences analysis of the use of the QUIPP app for triage and transfer compared to current practice. We hypothesise that there will be no negative impact on the health and wellbeing of women and neonates, as a result of the intervention, particularly given its non-invasive nature and that the intervention will be cost saving.

Women’s experience of TPTL assessment will be explored using self-completed questionnaires, with a subset of participants being invited to semi-structured interview.

